## Abstract

**Background:**

The causal relationship between high-risk (hr) HPV infection and precancerous lesions or cervical cancer has led to the development of strategies to increase screening performance and prevent this cancer. The increased sensitivity of DNA-HPV testing compared to cervical cytology favors DNA-HPV testing as a primary screening test. Cervical cancer screening in Brazil is opportunistic, and this cancer remains a considerable health problem with a high proportion of diagnoses in advanced stages. This paper aims to describe the design and implementation of the Cervical Cancer Screening Program with primary DNA-HPV testing (CCSP-HPV) planned for Indaiatuba City (SP), Brazil; the strategies to achieve higher population coverage; and a study protocol for cost-effectiveness analyses.

**Methods:**

The CCSP-HPV was designed based on successful guidelines that replaced cervical cytology-based screening by the DNA-HPV test performed at 5-year intervals. The screening will be performed for the female population aged 25-64 years cared for by the public health system and aim to reach 80% coverage after completing the first round. The chosen DNA-HPV test detects 14 hr-HPV types and genotypes HPV-16 and 18. All women with a negative test will be reassessed after five years. Women showing a positive test for HPV-16 and/or 18 will be referred for colposcopy. Those showing the other 12 hr-HPV types will be tested by cytology, and if any abnormality is detected, they will also be referred for colposcopy. The histopathologic evaluation will be reviewed by a pathologist panel and aided by p16 immunohistochemistry. A cost-effectiveness analysis will be performed by a Markov model comparing the cost of the new program and the screening performed by conventional cytology five years prior (2011–2016).

**Discussion:**

The new screening program is considered a breakthrough for public health regarding cervical cancer, which is the third leading cause of cancer death among Brazilian women. Achieving at least 80% coverage will have the possibility to change this scenario. The proposed program will provide a modern cervical cancer screening method for women, and information about cost-effectiveness will help other similar places support the decision of implementing cervical cancer screening using the DNA-HPV test.

## Background

Cervical cancer remains a major health problem, especially in developing countries such as Brazil [1, 2]. The widespread knowledge that cervical cancer is caused by persistent high-risk human papillomavirus (hr-HPV) infection has resulted in the development of biomolecular tests and alternative strategies for cervical preneoplastic lesion screening. Cytology-based cervical cancer screening (e.g. Papanicolaou test), colposcopy and histological diagnosis followed by the treatment of cervical intraepithelial neoplasms (CINs) have been widely used worldwide. Cervical cancer mortality reduction has been observed in high income and some middle-income countries, especially in those that have established successfully organized cancer prevention programs [3, 4].

However, in low- and middle-income countries, the success of screening is hampered by many factors, such as low cytology sensitivity, requiring frequent repetition to achieve longitudinal sensitivity, low coverage of the target population at regular intervals, and poor quality control of cytology services [3, 4]. These factors promote the search for alternative strategies, such as HPV molecular testing.

Several randomized clinical trials and prospective studies from the early 2000s to the present have shown the superiority of DNA-HPV testing to detect high-grade squamous intraepithelial lesions (HSILs), adenocarcinoma in situ (AIS) and early cervical cancer when compared to cervical cytology [5–9]. A meta-analysis study that included four European clinical trials concluded that screening with the DNA-HPV test may be conducted in women aged 30 years and older in at least five-year intervals [10].

The ATHENA study evaluated the Cobas® HPV test (Roche Molecular Systems, Pleasanton, CA, USA) as a primary screening test for cervical cancer in over 42,209 women, and the findings support the use of a combination of HPV-16/18 genotyping and reflex cytology only for the group of other hr-HPV positive, non-HPV-16/18 women for colposcopy triage. HPV-16/18 genotyping stratifies a high-risk group for HSIL/AIS, increasing the specificity of the test and making it possible to use it for screening starting at age 25 years, avoiding the implementation of hybrid strategies that use cervical cytology for younger women [9].

The DNA-HPV test has a negative predictive value of approximately 100% and allows a screening interval of at least five years, longer than the 3-year interval for cytology. These would reduce the total number of tests performed, affecting costs. Some studies have provided strong evidence for the adoption of the DNA-HPV test in cervical cancer screening [11–14].

The Food and Drug Administration (FDA), in April 2014, approved the DNA-HPV testing that includes genotypes 16 and 18 (Cobas® HPV) for primary screening of cervical cancer [15]. More recently, the Society of Gynecological Oncology and the American Society of Colposcopy and Cervical Pathology have proposed a guideline for cervical cancer screening based solely on the use of DNA-HPV tests for women over 25 years of age [16]. Australia also approved the primary screening of HPV, with colposcopic evaluation for HPV 16/18 and reflex cytology for other types of HPV, starting at 25 years of age and at intervals of five years when the result is negative for HPV [17].

Cervical cancer is the third most common cancer among women in Brazil, with an estimated 16,350 new cases in 2018 [18]. Current recommendations from the Brazilian Ministry of Health state that cervical cancer screening is based on cervical cytology, which should be repeated every 3 years after two consecutive annual negative examinations, in women aged 25-64 years [19]. Data show an excess of cytology due to the opportunistic screening currently practiced in Brazil, with approximately 50% of cervical cytology performed annually and only 10% within a three-year interval recommended by the Brazilian protocols. Additionally, approximately 20% of screening tests are performed on women under 25 years of age [20, 21]. Besides, there is a large proportion of cases diagnosed at advanced stages, most of them managed at Public Health System [21, 22]. These factors highlight the need for reassessment of the cervical cancer screening program currently in place in Brazil.

In 2017, the city of Indaiatuba, in São Paulo State, was the pioneer in Brazil deciding to replace cervical cytology with the primary DNA-HPV test for primary cervical cancer screening. This paper aims to describe the implementation of the *Cervical Cancer Screening Program with Primary DNA-HPV testing (CCSP-HPV)*, the strategies designed to reach higher population coverage, and a study protocol for the cost-effectiveness analyses.

## Methods/design

### Design, study setting and study population

This is a longitudinal study involving women from Indaiatuba (Sao Paulo State, Brazil), an urban city with a population of 240,000 people and a high (0.79) human development index [23]. The target women are women relying only on public health services (SUS – Unified Health System) and candidates for cervical cancer screening. Cervical cancer screening in Brazil includes women aged 25-64 years.

#### Sample size calculation

The female population 25-64 years old comprises 63,362 subjects for Indaiatuba, according to the official Brazilian Census (2010) and estimates for 2014 [24]. In Brazil, health care is free of charge to every citizen, although some people co-use private services. In Indaiatuba, around 50% of the female population uses private services, and the other half relies exclusively on the SUS to access health care. Therefore, the target SUS population was 31,681women for the new program. As the goal of the program is to reach at least 80% coverage of the target population after five years, the population of the study was estimated to be 25,000 women in five years, which means at least 5000 women tested per year.

The organization of the CCSP-HPV implies developing strategies to reach higher target population coverage, evaluate the compliance of the staff to the program, and research to evaluate the cost-effectiveness. For comparison, a similar population from the same city that performed routine cytology screening from 2012 to 2016, five years before CCSP-HPV will be the reference for comparison of cost-effectiveness evaluation. This reference population (years 2012–2016) performed nine to eleven thousand pap tests per year (total 54,000 to 66,000 tests), but with a low agreement, about 33%, with the official recommendations for pap screening.

### Eligibility

Inclusion criteria for CCSP-HPV
women have started sexual activity aged 25 to 64 years are the target for regular screening test (women over 64 years will be permitted for a single exit test by personal request);women physically well enough to undergo a pelvic exam.

The inclusion criteria evaluation should be postponed if any of the following conditions are met: 40 days postpartum period, abundant genital bleeding, cervicovaginal infection and having underwent the last cervical cytology in the last 12 months.

Exclusion criteria
women who have already undergone DNA-HPV testing for different medical purposes except screening;women with a previous diagnosis of the cervical lesion followed in specialized clinics;women who underwent a total hysterectomy.

Control group:
All women from Indaiatuba that underwent cytology tests by SUS from 2012 to 2016. These women will be identified from the regional central laboratory database, located at the Cytopathology Laboratory of Women’s Hospital (University of Campinas - UNICAMP). All information about the compliance of the staff to follow the official recommendations related to conducting the women with abnormal pap, as the follow-up and/or treatment, are available at Colposcopy Unit in Indaiatuba City and Women’s Hospital (UNICAMP).

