### Data analysis

Women’s information and test results will be entered into a single Excel database for the entire municipality. Some information will also be present in the Integrated Health Informatics System of Indaiatuba (SALUS System), which is a health management system for the entire city. A more detailed information system for monitoring screening population management according to the flowchart proposed for the CCSP-HPV protocol (schedule for sample collection, including follow-up cervical cytology and/or colposcopy, DNA-HPV test results, colposcopy, biopsy, EZT, and test repetition) is in development, which will be integrated into the SALUS System. Information will be discriminated for every primary health care unit. Thus, we will have the opportunity to monitor and identify areas with adequate population coverage and areas that need further action to achieve adequate coverage.

The databases with information generated from this protocol will be revised and analyzed annually and after the study ends. During the five years planned for the study, women inclusion and additional health procedures for those with positive HPV testing will be monitored every 30 days.

A cost-effectiveness survey is planned for this study, and it will be compared with the screening performed by conventional cervical cytology five years prior. Such analysis will also consider the diagnostic rates of precursor lesions and cervical cancer corresponding to the HPV test or cervical cytology-based periods. Indaiatuba public health system and regional health service (Women’s Hospital, UNICAMP) records will be reviewed looking for cases of HSIL, AIS or cervical cancer diagnosed and managed out of the screening set in women from Indaiatuba.

For cost-effectiveness analyses, the Markov model will be built, and the detailed process will be subject to future publication. Cost information regarding the screening process will be collected for the previous cytology screening and during the implementation of the new program.

Qualitative analysis is also foreseen to evaluate the perception of the population and health professionals regarding the modification of the method of cervical cancer screening in the city.

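### The cytology control group has no age range or exclusions to match the HPV group, so lesion detection rates and cost per lesion detected are not like for like

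*Protocol article*

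**What the plan says.** All of this is in the protocol article.

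- **HPV group (Eligibility).** The age criterion is "women have started sexual activity aged 25 to 64 years are the target for regular screening test", with one exception: "women over 64 years will be permitted for a single exit test by personal request". The exclusions include "women with a previous diagnosis of the cervical lesion followed in specialized clinics" and "women who underwent a total hysterectomy". Women already HPV-tested for non-screening reasons are also excluded, and women with cytology in the previous 12 months are postponed.
- **Control group (Eligibility).** The control is "All women from Indaiatuba that underwent cytology tests by SUS from 2012 to 2016". On the source it says: "These women will be identified from the regional central laboratory database, located at the Cytopathology Laboratory of Women’s Hospital". No age range, exclusion or screening-indication filter is stated. Follow-up and treatment information is said to be available at the Colposcopy Unit and the Women's Hospital.
- **Sample size calculation.** The reference is described as a similar population that had routine cytology screening. No criterion is given that would make it similar.
- **Use of the control (Data analysis).** "Such analysis will also consider the diagnostic rates of precursor lesions and cervical cancer corresponding to the HPV test or cervical cytology-based periods". No restriction, matching or standardisation is mentioned there.
- **Age mix.** Background states for Brazil that "approximately 20% of screening tests are performed on women under 25 years of age". The Discussion reports 7,362 HPV tests in the first 12 months, 99.1% of them in women aged 25–64.

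**The concern.** The two groups are defined side by side in one section, and only one of them carries eligibility rules. A detection rate depends on who is tested as well as on the test. Three differences follow from the control definition as it stands:

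- Women under 25 enter the control but cannot enter the HPV group. Their lesion risk may differ from that at 25–64.
- Women under specialised follow-up for a known lesion are not kept out of the control. If their follow-up smears are in the laboratory database, they could raise the apparent yield of cytology and its colposcopy workload.
- Women with total hysterectomy are not kept out either.

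This is the only comparator for the cost-effectiveness aim. A difference in lesion yield or cost per lesion between the periods could therefore partly reflect selection and be read as an effect of the test.

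**Working it through.** **1. The plan's own size for the HPV group.** From Sample size calculation: 63,362 × 0.50 = 31,681 target women; 31,681 × 0.80 = 25,345; 25,345 / 5 = 5,069 per year. This agrees with the stated 25,000 and 5,000 after rounding (25,000 / 31,681 = 78.9%). That figure is built on ages 25–64 only, unlike the control.

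**2. Control volume.** The same section gives 9,000–11,000 smears per year. Over the five years 2012–2016:

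- 5 × 9,000 = 45,000 and 5 × 11,000 = 55,000.

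The section states a total of 54,000–66,000, which equals six years (6 × 9,000 and 6 × 11,000). The Abstract gives the window as 2011–2016. That mismatch is a separate matter, so both totals are carried below.

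**3. Control tests under 25.** Assumption: the Brazil-wide share of about 20% applies in Indaiatuba.

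| Control total | Under 25 (× 0.20) | Remaining (× 0.80) |
|---|---|---|
| 45,000–55,000 | 9,000–11,000 | 36,000–44,000 |
| 54,000–66,000 | 10,800–13,200 | 43,200–52,800 |

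Tests over 64 cannot be quantified from the document.

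**4. HPV group for comparison.** 7,362 × (1 − 0.991) ≈ 66 first-year tests fell outside 25–64. So 0.9% were out of range at either end, against an assumed 20% under 25 alone in the control.

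**5. What the age mix could do to a rate (illustration).** Let s be the share of control tests under 25, and r the detection rate under 25 relative to that at 25–64. The document gives no r. The all-age control rate is the 25–64 rate multiplied by (1 − s) + s·r. Two equally performing tests would then show an HPV/cytology ratio of 1 / [(1 − s) + s·r].

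| s = 0.20 | Control rate multiplier | Apparent ratio |
|---|---|---|
| r = 0 | 0.80 | 1.25 |
| r = 0.5 | 0.90 | 1.11 |
| r = 1 | 1.00 | 1.00 |
| r = 1.5 | 1.10 | 0.91 |

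With s from 0.10 to 0.30 and r from 0 to 1.5, the ratio runs from 0.87 to 1.43.

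**6. What known-lesion follow-up could do (illustration).** Let a share f of control tests be follow-up of known lesions, with k times the detection rate. The control rate is then multiplied by (1 − f) + f·k. Both f and k are assumptions:

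- f = 0.01, k = 5: 0.99 + 0.05 = 1.04.
- f = 0.05, k = 20: 0.95 + 1.00 = 1.95.

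This would inflate the control by 4% to 95%. It acts against the age effect when r is below 1 and with it when r is above 1. Steps 5 and 6 use a per-test rate only for illustration, since the plan fixes no denominator.

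**The case against.** The strongest reply is that this is a before-and-after comparison of programmes. Out-of-age and repeat smears are the inefficiency that the new programme is meant to remove. Age compliance is a listed endpoint, and agreement with smear recommendations in the reference period was only about 33%. Trimming the control for total cost would erase a real effect. This stands in full for programme cost and age compliance. It does not reach lesion rates or cost per lesion.

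A second reply is that the Eligibility text names only a source population, and that analysis sets and the Markov model are left to other documents. It stands in part: the article fixes no per-test denominator, and it defines the control by woman. But the control definition is given, and it takes in all women tested. Describing the reference as similar and routinely screened states an intention that the definition does not carry out.

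A reader might also infer stronger points that the documents do not support:

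- *The bias cannot be undone later.* The control comes from an existing database, so a broad extract can still be filtered. Only hysterectomy and prior lesions may be hard to identify.
- *All cost comparisons are invalid.* Total programme cost is properly based on everyone tested.
- *Control women had 1.4–1.7 smears each, against one HPV test.* Dividing 45,000–55,000 by 31,681 gives 1.42–1.74, but sets all-age tests against women aged 25–64. With 20% removed it is 36,000–44,000 / 31,681 = 1.14–1.39. That is still per target woman, not per screened woman, and the HPV flowchart has its own repeat tests at 12 months and yearly.

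**Conclusion.** The point holds for lesion detection rates and cost per lesion detected. The age range and the lesion and hysterectomy exclusions of the HPV group are absent from the control definition, and no other section restores them.

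The age imbalance could be large: about one control test in five under 25, against fewer than one HPV test in a hundred outside 25–64. The control figure rests on the assumption that the national share applies locally. The numbers of women over 64, with known lesions or with hysterectomy in the control cannot be derived.

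Neither the size nor the direction of the net bias can be determined. The ratios of 0.87 to 1.43 and the inflation of 4% to 95% depend on assumed inputs, and the age effect vanishes if detection under 25 equals that at 25–64. A reader might infer that the comparison favours HPV testing, or that it favours cytology. The document supports neither.

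**What to change.** For lesion-rate and cost-per-lesion comparisons, amend the control definition and the Data analysis section as follows:

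1. Restrict both periods to women aged 25–64. This also sets aside the exit tests over 64 in the HPV group.
2. Apply the prior-lesion and hysterectomy exclusions to control records as far as laboratory and Colposcopy Unit records allow, and report how completely each could be identified.
3. Count per woman, starting from her first screening test in the window, in both periods.
4. Standardise both periods to a common age distribution.

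Keep the unrestricted all-women set, labelled as such, for total programme cost and age compliance.

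The Discussion announces a first interim cost-effectiveness analysis. The rules should be written down before it, so that the filter is not chosen with results in view.

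The cost is protocol wording plus filtering and de-duplicating an existing database. The control set becomes smaller: if the 20% share applies, 36,000–44,000 tests before the other restrictions and de-duplication (43,200–52,800 on the stated total). Hysterectomy and prior lesions will be imperfectly identified in older records, so some mismatch will remain and should be acknowledged.

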### Organization of the screening with primary DNA-HPV test and study procedures

#### HPV test selection

It should be noted that approximately 70% of invasive squamous carcinomas and 82% of adenocarcinomas are related to HPV-16 and/or 18 [25]. A study that analyzed data from more than 20,000 women for ten years showed the higher cumulative incidence of CIN3 in those women with initial infection of HPV-16 and/or 18 than in those infected with 11 other types of hr-HPV [26]. The availability of genotyping HPV-16 and 18 made it possible to evaluate the test performance for screening women aged 25 to 29 years and maintaining the same target age as the official Brazilian program. Considering these factors, the FDA-approved Cobas® HPV Test (Roche Molecular Systems, Pleasanton, CA) was defined as the HPV test for CCSP-HPV. This HPV test provides individual results on the highest risk genotypes - HPV 16 and HPV 18 - and aggregated results on the twelve other hr-HPV genotypes (types 31, 33, 35, 39, 45, 51, 52, 56, 58, 59, 66 and 68).

In addition to the DNA-HPV test, the sample vial will be stored for cytology evaluation, if necessary and according to the CCSP-HPV management flowchart (Fig. 1), preventing the women having to return for another sample collection.

**Fig. 1 Fig1:**
[figure not shown]
Overview of cervical cancer screening guidelines using a primary DNA-HPV test with HPV-16 and 18 genotyping in Indaiatuba City (SP), Brazil

For this study, the Cobas® HPV Test will be performed in a central laboratory, the Laboratory of Women’s Hospital (HPV Test Lab) located at the University of Campinas (UNICAMP), Campinas (SP), 45 km away from Indaiatuba. The Cobas® HPV Test runs on the advanced Cobas® 4800 System (Roche Molecular Systems, Pleasanton, CA, USA).

#### Defining the management flowchart

CCSP-HPV will last five years. The tests and laboratory will be the same for the entire five-year period planned for the study. Figure 1 represents the flowchart guiding CCSP-HPV. Briefly, the procedures are as follows:
Women with negative DNA-HPV tests will be instructed to return after five years to repeat the test.Women who test positive for HPV-16 and/or 18 will be referred for colposcopy.Women positive for the other 12 h-HPV types will also be evaluated by cervical cytology performed in the same sample. In the case of negative cervical cytology, women will return after 12 months to repeat the DNA-HPV test. If any abnormality was detected in cytology (ASC-US, LSIL, HSIL, suspicious for glandular lesion or cancer), the woman will be referred for colposcopy.

